# Palliative long-term abdominal drains vs. large volume paracentesis for refractory ascites secondary to cirrhosis: protocol for a definitive randomised controlled trial (REDUCe2 study)

**DOI:** 10.1186/s13063-025-08873-z

**Published:** 2025-06-04

**Keywords:** Ascites, End-stage liver disease, Paracentesis, Palliative care, Quality of life, Caregivers, Patient reported outcome measures, Cost-effectiveness analysis

## Abstract

**Background:**

Ascites remains the most common complication of cirrhosis and a frequent reason for hospitalisation in advanced chronic liver disease (ACLD). Ascites is associated with significant symptom burden, caregiver workload and poor health-related quality of life (HRQoL). Once refractory to treatment, median survival is poor. Many with refractory ascites (RA) will neither receive a transjugular intrahepatic portosystemic shunt (TIPS) nor a liver transplant. Palliative care remains underutilised and evidence-based interventions focused on improving HRQoL are clearly needed. The standard of care for RA is repeated hospital ascites drainage with large volume paracentesis (LVP). Our earlier feasibility randomised controlled trial (RCT) (REDUCe) showed acceptability of palliative tunnelled long-term abdominal drains (LTADs), as well as preliminary evidence of safety and efficacy. The current REDUCe2 trial is a definitive national study designed to assess the impact of palliative LTADs on HRQoL in patients with RA due to ACLD.

**Methods/design:**

The REDUCe2 study is a pragmatic, multicentre, open-label, mixed-methods, superiority RCT being conducted in England, Scotland and Wales. Patients with RA secondary to ACLD who are ineligible for a liver transplant or TIPS will be randomised 1:1 to receive a LTAD or continue the current standard of care (LVP). Fortnightly home research visits will be conducted for 12 weeks in both arms. The primary outcome will be liver specific HRQoL assessed at 12 weeks using the Short Form Liver Disease Quality of Life questionnaire (SFLDQoL). Secondary outcomes include assessment of symptom burden (Ascites Questionnaire), health utilities (EQ-5D-5L tool), caregiver workload (Caregiver Roles and Responsibilities Scale—CRRS questionnaire), safety (including infection, acute kidney injury and other clinical outcomes), health resource utilisation and acceptability of the intervention by patients, caregivers and healthcare professionals. We aim to recruit a total of 310 patients (155 in each arm).

**Discussion:**

Effective palliative care provision remains an unmet need in ACLD. The REDUCe2 study, the largest palliative interventional trial in the UK, aims to address this inequity for this vulnerable and underserved cohort. It has the potential to generate high quality evidence to optimise and enhance palliative care in RA.

**Trial registration:**

ISRCTN26993825, date registered: 15/08/2022.

**Supplementary Information:**

The online version contains supplementary material available at 10.1186/s13063-025-08873-z.

## Background 

Liver-related deaths in England have increased more than three-fold since 1971 [1], with hospital admissions due to liver disease rising by 51.5% in the financial year ending in 2023 compared to the previous decade [2]. Ascites remains the most common complication of advanced chronic liver disease (ACLD), and the main driver for hospitalisation [3, 4]. Refractory ascites (RA) is defined as diuretic-resistant ascites due to lack of response to optimal medical management, or diuretic-intractable ascites due to medication-induced side effects [5]. Up to one-third of patients with ascites will develop RA.[6, 7] Transplant free survival in RA remains poor [6–9]. Unfortunately, many with RA will neither receive a TIPS nor a liver transplant [7, 8, 10, 11].

Ascites is one of the main drivers of impaired health-related quality of life (HRQoL) in patients with ACLD [12–14]. Despite the poor prognosis associated with RA and the high symptom burden, only a minority of patients with ACLD receive palliative care, often only in the last days or weeks of life [8, 15, 16]. Poorer HRQoL in patients with cirrhosis and ascites independently predicts both the 12-month mortality as well as unplanned hospitalisation [9, 17]. In addition to the impact on patients’ well-being, ACLD has an impact on caregivers, who have a higher care burden, lower quality of life and higher incidence of anxiety and depression, compared with the general population [13, 18].

The current standard of care (SOC) for RA is repeated hospital attendance every few weeks for ascites drainage through a temporary drain (large volume paracentesis LVP) [19, 20]. Our Patient and Public Involvement (PPI) group describe feeling stigmatised in hospital, and LVPs as being “unbearably painful,” “devastating” and “traumatic.” Repeated hospitalisations could be particularly distressing if patients are confronting a life-limiting diagnosis. The SOC is also financially costly, a UK study of 45,000 individuals dying from cirrhosis, revealed that one-third required an LVP or more in their last year of life, costing the National Health Service (NHS) over £21,000 per person [21].

Palliative long-term abdominal drains (LTADs) are standard of care in malignant ascites [22–25]. These tunneled drains allow community nurses or caregivers to drain small volumes of ascitic fluid at home. Compared to LVP, LTADs have the potential advantage of improving HRQoL by reducing ascites-related-hospitalisation and improving symptom control and could also be cost effective [22–25]. Their use in ACLD, however, has been limited due to the scarcity of evidence, largely due to a perceived infection risk, especially peritonitis, and uncertainty regarding community management [26]. However, a recent systematic review [27], case series [28], as well as an earlier feasibility trial [29], have provided preliminary evidence of acceptability, safety, efficacy, and cost-effectiveness of LTADs in ACLD. Currently, pending definitive evidence, the National Institute for Health and Care Excellence (NICE) recommends the use of LTADs in ACLD only in the context of special arrangements (i.e. in research or closely audited practice) [30].

Delivering palliative interventional trials in ACLD can be challenging [31]. However, the lack of evidence-based interventions is a factor in the inequity of palliative care provision for patients with ACLD, hence the need for this trial.

## Methods/design

### Primary objective

The primary objective is to assess whether palliative LTADs result in better disease-specific HRQoL compared to LVP in patients with RA due to ACLD.

### Secondary objectives

Secondary objectives are to assess the impact of LTADs vs LVP on.Incidence of infection (especially peritonitis)Symptom burdenCaregiver workloadHealth resource utilisationGeneric HRQoLHealth utilities and cost per quality-adjusted life year (QALY)Perceptions of LTADs and LVP by patients, informal caregivers and healthcare professionals (HCPs) through qualitative interviews.

### Study design and setting

The REDUCe2 study is a mixed-methods, multicentre, open-label, superiority RCT being conducted in three United Kingdom (UK) nations (England, Wales and Scotland). Recruitment will take place over approximately four years with a three-month follow-up period for each participant. The study aims to recruit across 35 UK NHS Trusts (secondary/tertiary centres and district general hospitals), with a target sample size of 310 patients. Study sites participating in the trial at the time of manuscript submission are listed in Appendix 1. Follow-up research visits will take place in community settings (when possible) and will require close liaison between hospital-based research teams and local community partners.

### Characteristics of participants

The study participants will include patients with RA due to ACLD who are not currently candidates for liver transplantation or TIPS. Study inclusion and exclusion criteria are shown in Fig. 1. Non-English-speaking patients and those residing in long-term care facilities are also eligible. Participants in other trials can be recruited, provided there is no conflict between study protocols and the participant is not overburdened. Informal caregivers will be encouraged to take part in the study, but their absence will not preclude recruitment.

**Fig. 1 Fig1:**
[figure not shown]
Inclusion and exclusion criteria. Legend: Abbreviations: LTAD long-term abdominal drain, TIPS transjugular intrahepatic portosystemic shunt

### Participant timeline

The study timeline is shown in Fig. 2 along with a schedule of events detailed in Table 1.

**Fig. 2 Fig2:**
[figure not shown]
Participant flowchart. Abbreviations: ACLD advanced chronic liver disease, RA refractory ascites, PIS participant information sheet, LTAD long-term abdominal drain, LVP large volume paracentesis, SOC standard of care

**Table 1 Tab1:**
[figure not shown]
Schedule of events

Timepoints: visit windows calculated from baseline (+/-3 days)

*** **Randomisation once ascitic culture rules out peritonitis and eligibility confirmed.

† As per protocol – initially to drain 1-2 litres, two to three times a week, maximum of 5L a week

‡ To include reasons for TIPS/transplant ineligibility and assessment of alcohol and substance use

§ To include liver prognostic scores (Child Pugh score, MELD and UKELD) and liver complications such hepatocellular carcinoma, hepatic encephalopathy and variceal bleeding

¶ To include full blood count, urea and electrolytes, liver function tests, C reactive protein and INR. Haemostatic function to be corrected prior to LTAD insertion as per protocol

#Drainage record in LTAD group based on drain diaries, LVP group based on hospital records

*Abbreviations*
**–**
*LTAD* Long term abdominal drain, *LVP* Large volume paracentesis, *SFLDQoL* Short Form Liver Disease Quality of Life, *CRRS* Caregiver Roles and Responsibilities Scale, *AHCR* Ambulatory and Home Care Record

### Screening visit and consent

#### Screening visit

Prospective eligible patients will be identified through various pathways, including LVP day-case units, outpatient clinics, inpatients, multidisciplinary team (MDT) meetings, and palliative care referrals. A participant information sheet (PIS) will be provided to potential participants, and adequate time given for them to read and ask questions. If willing to participate, they will be invited to attend a hospital appointment and written informed consent will be received. For patients unable to provide written consent, verbal consent will be witnessed and countersigned by a third party according to Good Clinical Practice (GCP). Medical history, baseline data (including reasons for transplant/TIPS ineligibility) will be recorded and a diagnostic ascitic tap performed to exclude peritonitis.

Capacity regarding continuation in the study will be assessed at each follow-up visit. For those in England and Wales, verbal consent will be sought, and in case capacity is lost, a pre-agreed consultee (usually a caregiver) can be approached to ensure whether ongoing participation is in the patient’s best interest. For those in Scotland, the initial consent will be valid for the duration of the study, in accordance with Scottish law.

#### Caregiver consent

If available, and with the patient’s consent, informal caregivers will be approached and invited to participate in the trial. They will be given a caregiver PIS, after which written consent will be received for the questionnaire-based assessments and optional qualitative interview. Copies of the consent forms are included in Appendix 2.

### Randomisation

Once an ascitic tap has excluded peritonitis (defined as ascitic white cell count > 500 cells/mm^3^ or a neutrophil count > 250 cells/mm^3^ or a positive ascitic-fluid culture result)[19] participants will be registered by the local teams on an electronic data capture platform (Ennov:MACRO™) [32] and then randomised to receive either LTAD or standard of care (LVP) in a 1:1 ratio using Sealed Envelope™ [33]. The computer-generated software will confirm the patient’s treatment group allocation. The allocation will be minimised (i.e. dynamically generated) on sex and Child–Pugh Score (CPS) with an 80% probability of assigning participants to the group that balances these factors out. This will ensure comparability of the two groups. Only the trial manager, Chief Investigator (CI), and central research team will be aware of the exact sequence of the most recent allocations. Blinding researchers or participants is not feasible due to the nature of the intervention. However, the senior trial statistician will remain blinded until final data analysis, with adverse events (AEs) coded to prevent unintentional unblinding.

### Group 1 (LTAD)

Two routinely available LTADs will be used in the study. Rocket Medical plc (Watford, UK) Indwelling Peritoneal Catheters (IPCs)[34] and Becton Dickinson (New Jersey, USA) PeritX™ drains [35]. Choice of LTAD will be independently determined by each site’s research team.

#### LTAD insertion (baseline visit)

LTAD insertion must occur within 10 days of the ascitic tap. If this is not possible then a rescreening visit will be necessary to repeat the ascitic fluid analysis. Baseline assessments can be completed on the day of LTAD insertion. The procedure for LTAD insertion has been previously described [36], and will be performed by an interventional radiologist or an appropriately trained clinician. This is expected to be a day case procedure at most sites. Haemostatic parameters will be corrected according to local NHS trust policy prior to insertion. At sites where this is unavailable, patients will be transfused two units of fresh frozen plasma (FFP) when the international normalized ratio (INR) is ≥ 1.5 and up to two units of platelets if the platelet count is ≤ 50 × 10^9^/mm^3^.

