### Group 2 (LVP)

The control arm, intermittent LVP, is the current accepted SOC for managing patients with RA [19], typically performed in a dedicated medical day unit. Depending on site policy, patients require referral from an HCP or could self-refer for the procedure. The patient’s baseline visit will be scheduled to take place within 10 days of screening to coincide with an LVP visit in hospital.

The frequency of LVPs will depend on clinical need. Trained HCPs are expected to perform LVPs following national and local guidelines, as previously described [19]. Routine measurement of haemostatic function is not recommended [19].

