**Fig. 4 Fig4:**
[figure not shown]
CONSORT diagram. Abbreviations: n number, LTAD long-term abdominal drain, LVP large volume paracentesis

For the primary outcome, the analysis will follow intention-to-treat principles and will be conducted using a linear mixed effects model. All patients randomised through Sealed Envelope will be included in the group to which they were allocated regardless of the outcome or clinical trajectory.

This model will include fixed effects: time point, sex, Child Pugh score, randomisation group, and an interaction between randomisation group and time point, while adjusting for baseline SFLDQoL scores. A random effect for participant will be included to handle the correlation between repeated measurements across the study period. The model parameters will be estimated using restricted maximum likelihood, and treatment differences between groups at each follow-up will be reported along with 95% confidence intervals and p-values. Secondary outcomes will similarly be analysed using mixed effects regression models suited to the type of outcome.

Subgroup analyses will aim to stratify data based on patient and site-level characteristics. Patient-level factors will include liver prognostic scores baseline ascitic fluid protein level, socioeconomic status, and the presence of informal caregivers. Site-level data will include prior experience with LTADs, availability of dedicated LVP units, cirrhosis nurses, Palliative care MDTs for ACLD, and Improving Quality in Liver Services (IQILS) programme accreditation. Subgroup analyses will allow for the identification of potential effect modifiers or predictors of outcomes and changes in HRQoL.

Only in the case of significant protocol deviations, agreed with the CI, will participants be excluded from the final analysis. In accordance with MORECare guidance for palliative trials, attrition due to mortality, illness, and withdrawal will be detailed for each group [53]. Missing quantitative data will be assumed to be missing not at random (MNAR) unless evidence suggests otherwise. Imputation models will be utilised followed by sensitivity analyses using plausible adjustments to explore the potential impact of missing data and MNAR assumptions on treatment outcomes (multiple imputation with delta adjustment).

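### The text allows the baseline SFLDQoL, a covariate in the primary model, to be completed after open-label allocation is known, which could bias the adjusted difference

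*Protocol article*

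**What the plan says.** The Randomisation section and the notes to Table 1 give the order of events. The note reads "Randomisation once ascitic culture rules out peritonitis and eligibility confirmed". Eligible participants are registered "and then randomised to receive either LTAD or standard of care (LVP) in a 1:1 ratio". At that point "The computer-generated software will confirm the patient’s treatment group allocation", and the same section states that "Blinding researchers or participants is not feasible due to the nature of the intervention".

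The baseline visit is then described separately for each arm. The LTAD section is headed as both the insertion and the baseline visit, and says "Baseline assessments can be completed on the day of LTAD insertion". Under Group 2 (LVP), the "baseline visit will be scheduled to take place within 10 days of screening to coincide with an LVP visit in hospital".

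The Liver-specific HRQoL section places the first SFLDQoL at baseline, with repeats every four weeks. It also allows caregivers or researchers to supply proxy scores. The Statistical analysis section fits a mixed model to the follow-up scores "while adjusting for baseline SFLDQoL scores".

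The Screening visit section mentions recording baseline data but does not name the SFLDQoL. The body of Table 1 and Fig. 2 are not shown.

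**The concern.** A covariate is safe to adjust for when allocation cannot have affected it. A visit built around the allocated procedure normally comes after allocation, so a score taken there may already reflect it.

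Two routes are plausible. First, the patient, or the proxy, knows which treatment is coming. Several SFLDQoL domains (distress, hopelessness, stigma, symptoms) could respond to hope or disappointment, and the Background reports that the patient group finds LVP painful and distressing. Second, in the LTAD arm the form may be completed before or after insertion and the hospital drainage that follows it. The text does not say which, so procedural discomfort or relief after drainage could enter the score.

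If the baseline differs between arms because of allocation, the model treats that difference as chance imbalance and corrects for it. The primary estimate then gains or loses part of the treatment effect. An analysis plan cannot undo this, because it cannot turn a post-allocation measurement into a pre-allocation one.

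**Working it through.** **Inputs.** From Sample size calculation: target difference 8 points, SD 26.1, effect size 0.31, 93 analysed per arm, 90% power, 5% significance (two-sided assumed), baseline-to-follow-up correlation 0.48 (feasibility point estimate 0.77), three follow-up measurements, 40% attrition, 310 recruited. The documents give no figure for an allocation-induced baseline shift s, so s is an assumption, taken as 2 to 5 points.

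**1. The plan's own figure.** With one baseline, three follow-ups and all correlations 0.48, the variance factor for the adjusted mean of the follow-ups is (1 + 2 × 0.48)/3 − 0.48² = 0.6533 − 0.2304 = 0.4229. Then n per arm = 2 × (1.960 + 1.282)² × 0.4229 / 0.31² = 92.5, rounded up to 93. With the unrounded 8/26.1 it is 95. Allowing for attrition, 93/0.60 = 155 per arm, 310 in total. The plan's figure reproduces.

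**2. The bias.** The adjusted difference is (difference in follow-up means) − beta × (difference in baseline means). Under a clean baseline the second term has expectation zero. If allocation makes the expected baseline difference (LTAD minus LVP) equal to s, the adjusted difference is displaced by −beta × s. With equal SDs at baseline and follow-up (assumed), beta equals the correlation.

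| s (assumed) | beta 0.48 | beta 0.77 |
|---|---|---|
| 2 | 0.96 | 1.54 |
| 4 | 1.92 | 3.08 |
| 5 | 2.40 | 3.85 |

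As a share of the 8-point target, this runs from 0.96/8 = 12% to 3.85/8 = 48%. A simulation of 2,000 trials with 93 per arm and s = 5 gave mean bias of −2.39 (beta 0.48) and −3.93 (beta 0.77), in line with the formula.

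**3. Effect on the test.** At correlation 0.48 the standard error is 26.1 × √0.4229 × √(2/93) = 2.49. For s = 2, 4 and 5, two-sided type I error becomes 0.067, 0.120 and 0.161. If the bias runs against LTAD, power falls from 0.895 to 0.807, 0.685 and 0.614. These figures use the plan's variance for the mean of three follow-ups. For week 12 alone (standard error 3.36) the type I errors are 0.059, 0.088 and 0.110.

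**4. Cost of dropping the covariate.** Without the baseline score the factor is 0.6533 and the standard error is 26.1 × √0.6533 × √(2/93) = 3.09. Power for 8 points with 93 per arm is then about 74% at effect size 0.31 (73% with 8/26.1), against about 90% with adjustment.

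**The case against.** The strongest reply is that the timing is inferred. The table and flowchart that would fix the questionnaire's slot are not shown, the LTAD sentence is permissive, some baseline data are recorded at screening, and a journal article condenses a fuller protocol. This stands as far as certainty goes: a reader might infer that every baseline SFLDQoL is collected after allocation, and the documents do not establish that. It does not remove the point, because the article itself attaches the baseline visit to the allocated procedure and allows the assessments on that day.

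The size is also open. No shift is given in the documents, its sign is unknown, and domains such as memory or loneliness may barely move within days. That stands too, which is why a range is shown.

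Four stronger readings are tempting but not supported:

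- **Patients lost before the baseline visit drop out of the model, contradicting intention-to-treat.** The Statistical analysis section includes all randomised patients and plans imputation, with nothing limiting it to follow-up scores. Proxy scoring is also allowed.
- **Early events go uncounted.** Only visit windows are said to run from baseline. Harms and safety monitoring includes an end-of-study record review, and attrition from death, illness and withdrawal is to be detailed by group.
- **Follow-up starts at materially different times in the two arms.** Insertion is within 10 days of the screening tap and the LVP baseline within 10 days of screening. Both are hospital drainage attendances.
- **Rescreening applies only to LTAD and is therefore unfair.** Its stated purpose is to repeat the fluid analysis when insertion is delayed.

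**Conclusion.** The point holds as a risk to the primary estimate that is cheap to prevent, not as a demonstrated bias. The visible text permits an unblinded, self- or proxy-reported baseline to be given with allocation known and then used as the adjustment covariate. For an assumed between-arm shift of 2 to 5 points, the adjusted difference would be displaced by about 1.0 to 3.9 points, in either direction. This rests on the assumed shift, on equal SDs, and on slopes equal to the plan's two correlations. If forms are in practice completed before allocation is disclosed, the bias term disappears and only the wording needs correcting. The sample size is not at fault.

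**What to change.** **Remaining recruits.** State that the SFLDQoL and the other baseline questionnaires are completed after consent and before allocation is disclosed, for example at the screening visit. Recruitment was planned to run towards a last visit in September 2026, so this is useful only if made promptly.

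**Participants already randomised.** Record whether each baseline form preceded disclosure of allocation, and whether it preceded insertion or drainage. Report this by arm. Add a supportive sensitivity analysis of the primary outcome that omits the post-allocation baseline covariate and keeps sex and Child-Pugh score, which are fixed by the time of minimisation.

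**Cost.** A small amendment and a schedule change; 93 per arm and 310 in total stand. The baseline may be up to about 10 days older and less closely aligned with a drainage visit, with some possible loss of correlation. Participants recruited before and after the change will differ in baseline timing, which should be reported. Caregiver questionnaires at screening need the caregiver's consent by then, and caregivers are optional. The analysis without the covariate has only about 74% power on the plan's assumptions, so it should support the primary analysis rather than replace it.

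### The fallback platelet trigger before LTAD insertion is printed per mm³ instead of per litre, which makes it 10⁶ times too high

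*Protocol article*

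**What the plan says.** The rule is in the protocol article, under LTAD insertion (baseline visit). The default comes first: "Haemostatic parameters will be corrected according to local NHS trust policy prior to insertion". The fallback follows: "At sites where this is unavailable, patients will be transfused two units of fresh frozen plasma (FFP") at an INR of 1.5 or more, and "up to two units of platelets if the platelet count is" ≤ 50 × 10⁹/mm³, with both exponents printed as superscripts.

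No other part of the article gives a platelet threshold. The footnote to Table 1 says only "Haemostatic function to be corrected prior to LTAD insertion as per protocol" and states no figure. The section on Group 2 (LVP) advises against routine clotting checks and gives no threshold. The Randomisation section uses the per-mm³ unit properly, with a plain count: "a neutrophil count > 250 cells/mm^3".

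**The concern.** A platelet count may be written as a multiple of 10⁹ per litre or as a multiple of 10³ per mm³. The article takes the multiplier from the first form and the unit from the second. The result is not a count that blood can have, so as a decision rule it separates no patients: everyone falls below it.

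What is at stake is an instruction to give a blood product before the trial procedure, in patients with advanced liver disease. The fallback wording is directive, and it is meant for sites that have no local policy against which to check it. Statistical inference is not at stake.

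**Working it through.** **Inputs**

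- Printed trigger: ≤ 50 × 10⁹ per mm³ (LTAD insertion (baseline visit)).
- Planned LTAD arm: 155 of 310 participants (Abstract, Methods/design).
- Conversions: 1 L = 10⁶ mm³; 1 mm³ = 10⁹ fL.

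**1. The printed figure per litre**

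50 × 10⁹/mm³ × 10⁶ mm³/L = 5 × 10¹⁶/L, which is 50,000,000 × 10⁹/L.

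**2. The two natural repairs**

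| Repair | Calculation | Result |
|---|---|---|
| A: change the unit, 50 × 10⁹/L | 50 × 10⁹ ÷ 10⁶ | 50,000/mm³ |
| B: change the multiplier, 50 × 10³/mm³ | 50 × 10³ × 10⁶ | 5 × 10¹⁰/L = 50 × 10⁹/L |

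A and B are the same threshold, so the correction does not depend on which symbol was mistyped.

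**3. Size of the error**

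5 × 10¹⁶ ÷ (5 × 10¹⁰) = 10⁶.

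**4. Can the printed value occur?**

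Volume of blood per platelet at the printed threshold: 10⁹ fL ÷ (50 × 10⁹) = 0.02 fL. This is physically impossible.

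**5. What the literal rule does**

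| Count (× 10⁹/L) | Per mm³ | Meets the printed trigger? | Meets ≤ 50 × 10⁹/L? |
|---|---|---|---|
| 20 | 20,000 | yes | yes |
| 50 | 50,000 | yes | yes |
| 100 | 100,000 | yes | no |
| 150 | 150,000 | yes | no |
| 400 | 400,000 | yes | no |
| 1000 | 1,000,000 | yes | no |

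**6. How many insertions the fallback could cover**

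155 × (share of insertions at sites without a local policy). The article does not give that share. Over its full range of 0 to 1, the result is 0 to 155 planned first insertions, or 0% to 50% of 310 participants. This is the reach of the rule and not a count of patients who would be wrongly transfused.

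**7. Could text extraction explain it?**

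Both exponents are explicit in the text, on the 10 and on the mm. A lost superscript does not account for the printed form.

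**The case against.** The strongest reply is that this is a unit slip with no plausible consequence. Local trust policy governs, and the printed number matters only where no such policy exists. The drain is placed by a radiologist or another trained clinician, who would see at once that 50 × 10⁹/L is meant. Sites also work from the approved protocol (v9.0 according to Trial status) and study procedures, none of which is shown, so the slip may exist only in the journal article. The range of 0 to 155 says nothing about actual harm, and a factor of one million measures the misprint and not any clinical effect.

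Most of this stands, and it is why the point ranks low. Nothing in the article shows that the form recurs elsewhere or that any patient has been or will be over-transfused. What does not follow is that the figure may stay. That the intention is easy to guess limits the severity, but the printed value is still wrong. It is the only platelet threshold in the article, and it sits in an operative instruction and not in background text.

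**Conclusion.** The concern holds as a minor point. The fallback platelet trigger is wrong as printed by a factor of exactly 10⁶, and the intended value is 50 × 10⁹/L (50,000/mm³). The size of the error rests only on unit conversion. The intended value rests on the two simplest repairs agreeing.

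The consequence is limited to the LTAD arm at sites without a local policy, whose number is not stated. The expectation that over-transfusion is unlikely, and may be nil, assumes that clinicians read the figure as intended. The INR trigger in the same sentence is unaffected, as are the sample size, the endpoints, the primary analysis and the error rates.

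**What to change.** Under LTAD insertion (baseline visit), print the trigger as ≤ 50 × 10⁹/L, or equivalently ≤ 50 × 10³/mm³, after confirming the value against the full protocol. If the printed form also appears in the full protocol or in any site document, correct it there. Last patient last visit is planned for September 2026, so a correction can still reach sites.

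The cost is one line of text and a short document check. Design, sample size and analysis do not change.
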